### Interim analyses {21b}

No interim analyses are planned for this trial.

### Methods for additional analyses (e.g., subgroup analyses) {20b}

While not formally powered to examine subgroup differences, we will analyze change in FSCs after each dietary intervention by covariates such as age, sex, and baseline value of the outcome.

### Methods in analysis to handle protocol non-adherence and any statistical methods to handle missing data {20c}

Data from all randomized participants will be analyzed using intention-to-treat. Compounds with more than 90% missing over all plasma or urine samples will be removed. Remaining compound values will be log2 transformed, and data will be corrected for batch and order effects using residuals from linear regression with FSC abundance as the outcome with order, batch, and order by batch interactions as predictors after removing outliers and values below the detection limit (i.e., missing). Outliers will be defined as having residuals from the model that are more than the third quartile plus 1.5*interquartile range or less than the first quartile minus 1.5*interquartile range. The resulting linear model will be used to predict compound values for all observations (i.e., including outliers). After batch and order correction, QC values will be shifted by the minimum observed value for each compound, and compounds with a high coefficient of variation (CV ≥ 0.3) for QC values will be removed. Given the expectation of meaningful and real zero values (i.e., in baseline plasma samples) and arbitrary quantities of untargeted metabolomics, adjusted values will be ranked within each compound to enable parsimonious inclusion of zero values. Missing values will be given the lowest ranks. In case of multiple missing values or duplicate normalized values, an average of ranks will be assigned.

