### Trial design {8}

This trial is a 16-week randomized, multi-intervention, semi-controlled feeding study of Mediterranean-amplified (mini-MED) and habitual/Western-style (Western) isocaloric dietary interventions containing 500 kcal/day from target foods. Participants are randomized (1:1) to start either the mini-MED or the Western dietary intervention, with subsequent assignment to the other upon completion of the first. Each 4-week intervention (mini-MED and Western) is repeated once. The Western intervention serves as both a washout of the mini-MED foods and a negative control for the postprandial response when the mini-MED foods are not consumed. Within the mini-MED arm, participants are further randomized to first receive salmon (mini-MED salmon) or lean, unprocessed beef (mini-MED beef) as a protein source, with consumption of the alternate protein source in their second mini-MED intervention period (Fig. 1). Outcome measures and biospecimen sampling take place at baseline and intervention weeks 4, 8, 12, and 16, and outcomes will be assessed using an exploratory approach.

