Refined grain	Refined grain bread	56	5

Food-specific compounds identified in foods and plasma from the completed MED controlled feeding intervention provide mini-MED and Western target foods for evaluation of reproducibility within the mini-MED intervention

^a^Participants consume salmon as a protein source during the mini-MED salmon arm

^b^Participants consume lean, unprocessed beef as a protein source during the mini-MED beef arm

^c^Cheesecake is included in the target food list for the Western diet but was not included in the original MED controlled feeding intervention and, as a complex food, was not analyzed using metabolomics and thus food-specific compound data are not available (N/A)

**Table 2 Tab2:** Serving size and energy density of target foods provided during the mini-MED study

Food	kcal per 100 g	Serving size	kcal per serving	Form(s)	Servings per week	kcal per week
*mini-MED target foods*						
Cherry	63	½ cup (75 g)	47	Frozen, unsweetened	7	329
Avocado	167	1/3 total (45.3 g)	76	Raw, California	6	456
Red bell pepper	26	½ cup, chopped (74.5 g)	20	Raw	7	140
Basil	23	2 Tbsp	5	Fresh	5	25
	233	1 tsp	2	Dried	Varies	10
Walnut	654	½ oz (14.18 g)	93	“English”	6	558
Chickpea	139	1/3 can (84.3 g)	117	Canned, drained solids	6	702
Oat	379	1/3 cup (27 g)	102	Oats, regular and quick, dry	6	612
Salmon^a^	208	4 oz (113 g)	236	Atlantic, farmed, raw	3	708
Beef^b^	176	4 oz (113 g)	199	Ground, 90% lean meat, 10% fat, raw	2	398
	246	4 oz (113 g)	278	Beef, tenderloin, steak, separable lean and fat, trimmed to 1/8″ fat, choice, raw	1	278
**Total energy intake per week (kcal/week)**						** ~ 3500**
*Western target foods*						
Beef	176	4 oz (113 g)	199	Ground, 90% lean meat, 10% fat, raw	2	398
	246	4 oz (113 g)	278	Beef, tenderloin, steak, separable lean and fat, trimmed to 1/8″ fat, choice, raw	1	278
White potato	77	1 medium potato	164	Potatoes, flesh and skin, raw	5	820
Sour cream	198	1 Tbsp	24	Cream, sour, cultured	7	168
Chocolate frozen yogurt	131	1 cup	228	Frozen yogurts, chocolate	4	912
Cheesecake	321	1/6 of 17 oz cake (80 g)	257	Cake, cheesecake, commercially prepared	2	514
Refined grain bread	321	1 roll	93	Rolls, dinner, sweet	5	465
**Total energy intake per week (kcal/week)**						** ~ 3500**

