#### Sample size {14}

Most of our planned analyses use each individual as their own control by looking at the change over each dietary intervention period. This reduces between subject variability compared to a cross-sectional analysis and increases the statistical power at a given sample size. To obtain a reasonable minimum expected effect size for the mean difference divided by the standard deviation of the difference (i.e., Cohen’s *d* effect size), we used our analysis of salmon FSCs [13]. The minimum salmon FSC effect size that passed an FDR adjustment was 0.45. Using a paired *t*-test after consuming the food, a sample size of *N* = 20 was needed to achieve 80% power for this effect size of 0.45 and a Bonferroni multiple testing adjustment for the number of compounds that increased in the preliminary MED data (*N*_compounds_ = 21; *p*-value_adjusted_ = 0.05/21 = 0.0024). We assume a 10% loss to follow-up based on our experience in similar dietary intervention trials and therefore enroll *n* = 22 eligible individuals to have *n* = 20 individuals complete the trial.

We also evaluated the power of *N* = 20 sample size further using the Bonferroni adjustment for the 21 compounds that increased after consumption of the preliminary Mediterranean diet foods (*p*_adj_ = 0.0024) and a stricter adjustment using all 355 compounds that were detected in the MED foods and plasma (*p*_adj_ = 0.05/355 = 0.00014). For both significance thresholds, we achieve power across a range of relevant effect sizes (Fig. 2) including nearly 100% power to detect an effect size of 0.75 (the median effect size for the salmon FSCs that passed the FDR threshold).

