### Assignment of interventions: allocation

#### Sequence generation {16a}

All participants complete the mini-MED and Western dietary interventions twice each for four total intervention periods. Participants are randomized (1:1) to start either the mini-MED or Western dietary interventions, with subsequent assignment to the other upon completion of the first. A second randomization within the mini-MED arm is conducted to allocate participants to order of consumption of either salmon or lean, unprocessed beef as a protein source resulting in a total of four possible intervention orders (Fig. 1). Lean, unprocessed beef is consumed as the protein source in both Western intervention periods. A permuted block randomization scheme and stratification by sex has been generated and is utilized to ensure balance between intervention order and number of males and females. The allocation sequence was generated using computer-generated random number sequence in R using the *sample* command in *base* R package.

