##### Biospecimen sampling

At monthly in-person assessment visits at the CTRC, participants complete several biospecimen collections:*Fasting blood draw*: Trained phlebotomists use standard sterile techniques to collect approximately 35 mL of venous blood into Vacutainer tubes with appropriate additives for specific tests (e.g., EDTA collection tubes for plasma analysis). Trace metal-free materials are used for all blood collection, processing, and storage. Samples are collected after 12-h fast at five time points throughout the intervention (pre- and post- each intervention). Samples will be used for analysis of specific outcome measures, including FSCs and cardiometabolic health indicators such as lipids, lipoproteins, inflammatory markers, and adipokines (described below). Blood collected for plasma carotenoid assessments is immediately covered with foil to protect from light and maintained on ice prior to processing.*24-h urine sample*: Participants are asked to collect a 24-h urine sample the day prior to each in-person data collection visit (aligning with the final day of 3-day diet record collection). Briefly, participants are asked to start collecting urine after their first morning void on the day prior to in-person visits. All urine is collected using the materials provided (toilet hat, pre-labeled and pre-weighed 4 L high-density polyethylene (HDPE) jug) after this time and up until the first morning void the morning of the assessment visit, representing a full 24-h period. Urine is stored in a cool, dark place or refrigerated in the participants’ home refrigerators at approximately 4 °C between voids. Participants record start and end times and dates prior to placing in the provided cooler with ice pack for transport to the CTRC. Total urine volume is determined by weight, and samples are processed immediately to separate into aliquots, frozen on dry ice, and transferred to longer-term storage at − 80 °C for planned batch analyses at study completion.*First morning void spot urine samples*: Participants collect 10–20 mL urine from their first morning void (FMV) for two days prior to and the morning of in-person data collection visits (including a small amount of urine not included within the 24-h urine sample) using a pre-labeled urine collection container. This aligns with days 2 and 3 and the day after 3-day diet record collection for a total of three FMV samples. Participants are asked to place their urine sample into their home freezer at approximately − 20 °C immediately after collection and to transport the sample in the provided cooler with ice pack to in-person visits at the CTRC. Samples are thawed on ice and processed immediately to separate into 2 mL aliquots and placed at − 20 °C prior to subsequent transport on dry ice to longer-term storage at − 80 °C for planned batch analyses at study completion.*Fecal sample*: As close as possible prior to each in-person data collection visit, participants are asked to collect stool into the provided toilet hat and transfer to a pre-labeled fecal collection container using the provided collection tool/spatula and gloves (EasySampler® Stool Collection Kit, ALPCO Diagnostics, Salem, NH, USA) after training by research personnel. Participants record collection times and dates and place samples immediately in a home freezer at approximately − 20 °C upon collection. Participants are advised not to collect samples if taking certain medications (e.g., laxatives, antibiotics) or if experiencing diarrhea. Participants transport samples to the CTRC in the provided cooler with ice pack. Samples are thawed and processed immediately to separate into aliquots, frozen on dry ice, and stored at − 80 °C for planned batch analyses at study completion.*Skin carotenoids*: Participant skin carotenoids are assessed noninvasively at each in-person assessment visit using the Veggie Meter® (Longevity Link Corporation, Salt Lake City, UT, USA), which is a research-grade instrument that detects and quantifies carotenoids in the skin through the use of pressure-mediated reflection spectroscopy [32]. Procedures follow the published recommendations for use of the Veggie Meter® in the research setting [32]. Briefly, participants are asked to wash hands with soap and water, and skin carotenoids are measured on the nondominant ring finger in triplicate. The average of three scan values, each lasting approximately 30 s, will be used for all analyses. Skin carotenoids have been validated against plasma carotenoids and used as a proxy for fruit and vegetable intake in several studies [33].*(Optional) EnteroTracker® upper GI sampling device*: The EnteroTracker® is a novel, minimally invasive device developed at the University of Colorado for sampling the proximal gut that allows for the capture of samples from the upper GI tract and thus permits monitoring and study of the duodenal and jejunal microbiome, metabolome, and nutritional biomarkers. Externally, the 2-cm capsule device contains a slim, non-absorbent tethering string extending out of its end. Internally, it is a composed of a proximal, tethering string and a distal, collection string that are of different thicknesses and textures. This device is FDA class 1 510(k) exempt and cleared for commercial use for GI sampling. Participants have the option to complete the EnteroTracker® sampling pre- and post- each dietary intervention. Those choosing to participate are asked to refrain from use of mouthwash the morning of the visit where the EnteroTracker® device will be used. Briefly, when the intact capsule is swallowed, the tethering string is taped to the cheek. As the capsule passes through the upper GI tract, it deploys the collection string along the length of the esophagus, stomach, duodenum, and jejunum. The collection string then gently rubs on the epithelial surface obtaining a liquid biopsy from the mucosa. Dwell time for the string assessment is at least 1 h and no more than 4 h. Upon retrieval through the mouth, geographic localization of string samples is identified by (1) position along the length of the string (esophagus 0–45 cm, stomach 45-–65 cm, duodenum 65–90 cm, jejunum > 90 cm), (2) colorimetric changes on the collection string associated with changes in pH, and (3) presence of bile staining as an objective indicator of localization in the small intestine. Samples of the collection string corresponding to each segment are processed for planned microbiome assessments (e.g., 16S rRNA gene profiling, metagenomics). Previous studies have shown the EnteroTracker® is easily performed by a research assistant and well tolerated by patients, preferred over endoscopy, and thus highly suitable for repeated, unsedated, clinical and research sampling [34].

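### The 90% missingness filter is pooled over all samples, so it sets a stricter detection bar for salmon compounds than for the other foods and can remove some of them untested

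*Protocol article*

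**What the plan says.** The rule is in the section on non-adherence and missing data {20c}: "Compounds with more than 90% missing over all plasma or urine samples will be removed". It is not split by food, diet, period or visit. The same section equates missing values with values below the detection limit. It then says that genuine zeros are expected, for example in baseline plasma, and gives missing values the lowest ranks.

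The feeding schedule comes from three places. Trial design {8} gives salmon or beef in the first mini-MED period, "with consumption of the alternate protein source in their second mini-MED intervention period". Sequence generation {16a} adds: "Lean, unprocessed beef is consumed as the protein source in both Western intervention periods". Table 2 supplies salmon as three servings a week. For the blood draws, Biospecimen sampling says: "Samples are collected after 12-h fast at five time points throughout the intervention". The number of participants is in Sample size {14}: "enroll *n* = 22 eligible individuals to have *n* = 20 individuals complete the trial".

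**The concern.** The background section sets out the premise that an FSC is found after its food is eaten and is not found otherwise. A compound that behaves this way is missing in most samples by design. The ranking step treats those absences as information, but the filter before it counts them against the compound.

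The filter also bears unequally on the foods, because each food is fed before a different share of the draws. Salmon has the smallest share. It is also eaten on only some days of the week, and no passage ties those days to the visit. A removed compound is never tested, so the loss would not show among the tested results. Salmon has the most plasma-detected compounds in Table 1 (143), and the sample size rests on salmon FSC effect sizes.

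**Working it through.** **Inputs.** 22 enrolled and 5 draws each give 110 plasma samples (20 completers give 100). Each participant has one salmon period, two mini-MED periods with the plant foods, and three beef periods (one mini-MED, two Western). So 22, 44 and 66 samples follow salmon, plant-food and beef feeding. Salmon is supplied 3 times a week. The article gives no detection window, background detection rate or removal probability, so those below are assumptions and there is no stated figure to reproduce.

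**Cut-off.** With 10 detections, (110 − 10)/110 = 90.9% are missing and the compound is removed. With 11, (110 − 11)/110 = 90.0% and it is kept. For 100 samples, 9 is removed and 10 is kept.

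**Implied bar at fed visits, if the compound is absent elsewhere.** This step needs no kinetic assumption.
- Salmon: 11/22 = 50%
- Plant foods: 11/44 = 25%
- Beef: 11/66 = 17%

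**Removal probability for salmon, no background.** P(X ≤ 10) with X ~ Binomial(22, p):

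| Assumption | p | Removed |
|---|---|---|
| One-day window, salmon days unrelated to visit days | 3/7 | 68% (67% with 20 completers) |
| 50% detection | 0.50 | 42% |
| 60% detection | 0.60 | 12% |
| Two-day window, random days: 1 − C(4,2)/C(7,2) = 15/21 | 5/7 | 0.9% |

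**Same, with background.** Keep p = 3/7 and add Binomial(88, b) detections at the other four visits. Removal is 54% at b = 1%, 41% at 2%, 29% at 3% and 14% at 5%.

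**Plant-food comparison.** P(Binomial(44, 0.5) ≤ 10) = 0.02%, and at p = 3/7 it is 0.4%. Equal detection at fed visits therefore carries very different removal risks: 42% against 0.02% at one half.

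**Could a removed compound have passed the trial's own rule?** The statistical methods {20a} require a significant increase over mini-MED and a significant decrease over Western, after FDR. As an approximation, treat each detection as one unit of change and all other changes as zero, and use a one-sample t on 44 changes, with q the share that change: t = q / √(q(1 − q)/43).
- Increase: 10 detections give q = 10/44 = 0.227, t = 3.56, p = 0.0009; 8 give t = 3.09, p = 0.0035.
- Decrease: one of the four orders (Western, beef, Western, salmon) has no Western period after salmon, so about three quarters of the detections can show a fall. Seven give t = 2.85, p = 0.007; six give t = 2.61, p = 0.013.

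Such a compound could pass FDR, depending on the other compounds tested, yet with 8 to 10 detections in all it is removed first.

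**Under a food-specific filter.** Salmon has 22 × 2 = 44 pre and post samples. A compound is removed at 4 detections (90.9% missing) and kept at 5 (88.6%). P(Binomial(22, 3/7) ≤ 4) = 1.4%, against 68%.

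**The case against.** The strongest reply is that the 68% sits in one corner of the assumptions. It needs a window of about one day, three salmon days unrelated to the visit, and no detection in the other 88 samples. Relaxing any one lowers it: about 1% with a two-day window, 19% if the three servings are spread over four days (p = 4/7), 14% with 5% background. Some background is plausible. Participants are omnivores who otherwise keep their usual diet, and the instruction to avoid foods covers only the opposite arm's foods, so salmon is not clearly barred in the mini-MED beef period. This stands. A reader might infer that a valid salmon FSC is likely to be discarded; the documents do not support that, because they fix none of these inputs.

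A second reply is that a compound absent from the fasting plasma of more than half the participants after four weeks of salmon is a weak marker by the protocol's own standard of reproducible detection. This stands in part. It rules out saying that removal has nothing to do with marker quality. It does not explain why the same detection rate should keep a plant-food compound and drop a salmon one.

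Third, Table 1 lists 143 salmon compounds in plasma, and nothing shows how many are short-lived, so harm to the validation of salmon as a food is not shown. That also stands.

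Fourth, the batch and order correction is fitted after values below detection are dropped. If it is fitted to participant samples, two batches with order and interaction terms already need four parameters and three need six. A rule that keeps compounds with 5 detected values can leave that model nearly saturated. This is a real cost, and the fix has to meet it.

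**Conclusion.** The concern holds as a structural one. The pooled filter sets a bar of about 50%, 25% and 17% detection at salmon-fed, plant-fed and beef-fed visits. That follows from the design and the rule alone, and the article gives no reason for a bar three times as high for salmon as for beef. As a result a salmon FSC can be removed untested.

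How often depends on quantities the article does not give. The removal probability runs from about 68% (one-day window, unrelated days, no background) to about 1% (two-day window), with the 50% and 60% detection cases and the background cases in between. Confidence is high for the unequal bar and low for the number of compounds lost. The rule is worth correcting because samples are to be analysed in batch at study completion and no interim analysis is planned, so it can be settled before the metabolomics data exist.

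**What to change.** For each food's pre-defined FSCs, apply the 90% rule to the pooled pre and post samples of the periods in which that food is supplied. Salmon then has 44 samples, 22 of them after feeding, and the plant foods 88, with 44 after feeding. Both need 5/22 = 23% and 9/44 = 20% detection at fed visits, so the bars are close to equal. Because pre and post samples are pooled, the filter stays blind to the increase being tested. For the Western decrease the blindness is only approximate, since for salmon just one end of a Western period falls in the pool.

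State as well a minimum number of detected values, set from the number of batches and the terms in the correction model, below which a compound is not analysed whatever its food.

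Cost: a few lines of code and a sentence in the plan. More salmon compounds enter the FDR family, so its threshold becomes slightly stricter, and the batch and order correction is less stable for the sparsest compounds retained. The stated minimum limits the second cost.

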### Outcomes {12}

The primary outcome for this clinical trial is change in the relative abundance of FSCs from beginning to the end of each dietary intervention period in participant plasma samples. Secondary outcomes include detection of FSCs in participant urine samples as well as mean changes in cardiometabolic health indicators (e.g., total cholesterol, LDL cholesterol, HDL cholesterol, triglycerides, insulin, glucose, systolic and diastolic blood pressure), inflammatory markers (e.g., C-reactive protein, interleukin-6, tumor necrosis factor-alpha, alpha-1-acid glycoprotein), and adipokines (e.g., leptin, adiponectin) over each dietary intervention. Exploratory outcomes include changes in diversity and community composition of the gut microbiota over each dietary intervention period.

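### The quality-control CV cut-off of 0.3 is applied to log2 values shifted by a minimum, so it is not a limit on assay precision

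*Protocol article*

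**What the plan says.** Section {20c} of the protocol article, on non-adherence and missing data, sets out the metabolomics processing in order.

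1. Scale and correction: "Remaining compound values will be log2 transformed, and data will be corrected for batch and order effects using residuals from linear regression". Outliers and values below the detection limit are left out of that fit.
2. Application to everything: "The resulting linear model will be used to predict compound values for all observations (i.e., including outliers").
3. Shift, after the correction and leading straight into the filter: "QC values will be shifted by the minimum observed value for each compound, and compounds with a high coefficient of variation".
4. Filter: "compounds with a high coefficient of variation (CV ≥ 0.3) for QC values will be removed".
5. Ranking, as a later and separate step: "adjusted values will be ranked within each compound to enable parsimonious inclusion of zero values".

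No step between 1 and 4 returns the values to the abundance scale. Step 3 does not say whether the minimum is taken over the QC samples or over all samples of the compound.

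The compounds that survive step 4 supply the primary outcome in Outcomes {12}, "change in the relative abundance of FSCs from beginning to the end of each dietary intervention period in participant plasma samples". They also make up the set over which the false discovery rate is controlled in Statistical methods {20a}.

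**The concern.** A coefficient of variation is an SD divided by a mean, and it describes precision only on a scale with a true zero. Abundance has one. Batch-corrected log2 values do not: least-squares residuals centre near zero, so their mean says nothing about how much compound is present. Shifting by the minimum makes the mean positive, but the denominator then becomes the distance from the QC mean to whichever value was lowest. The threshold of 0.3 looks like a familiar limit on assay precision, but it is compared with a different quantity.

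At stake is which food-specific compounds reach the primary analysis and how many tests the false discovery rate adjustment covers. The later ranking is unaffected by the shift, but it cannot restore a compound already removed or take out one wrongly kept.

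**Working it through.** The cut-off is a rule, not a derived figure, so there is nothing to reproduce. The check is what the rule means under each reading of the minimum.

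**Inputs**
- From the document: log2 scale, shift by the minimum, cut-off 0.3.
- Study plasma samples: 22 enrolled (Sample size {14}) × 5 visits = 110.
- Assumed, because not given: the number of QC samples (10 to 200; 12 in the all-sample simulation), the between-sample SD of a compound (0.2 to 3 log2 units), and normal errors on the log2 scale.

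**Link between the scales.** For lognormal error, CV = sqrt(exp((ln2 × SD_log2)²) − 1). Inverted at CV = 0.30: SD_log2 = sqrt(ln(1 + 0.09)) / ln2 = 0.2936 / 0.6931 = 0.424.

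**The protocol's statistic**, reading the shift as subtraction: ratio = SD(QC) / (mean(QC) − minimum).

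**Reading A: minimum over the QC samples.** Multiplying every QC deviation by a constant multiplies numerator and denominator alike, so precision cancels. In simulation, QC SDs of 0.1 and 1.0 log2 units give the same results to within simulation error:

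| QC samples | Median ratio | Share passing (ratio below 0.3) |
|---|---|---|
| 10 | 0.64 | 0% |
| 20 | 0.54 | about 0.1% |
| 50 | 0.45 | about 1% |
| 200 | 0.37 | 7 to 8% |

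**Reading B: minimum over all samples.** Let D be the distance in log2 units from the QC mean to the lowest value. The cut-off then falls at SD_log2 = 0.3 × D.

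| D | Ratio for a compound with true CV 30% (0.424 / D) | Raw CV at which the cut-off falls |
|---|---|---|
| 0.5 | 0.85 | 10% |
| 1 | 0.42 | 21% |
| 2 | 0.21 | 43% |
| 3 | 0.14 | 69% |
| 4 | 0.11 | 100% |
| 6 | 0.07 | 193% |

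Worked line for D = 3: 0.3 × 3 = 0.9; 0.9 × 0.6931 = 0.624; sqrt(exp(0.389) − 1) = 0.69. The rule means a raw CV of 30% only when D = 0.424 / 0.3 = 1.41.

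Simulated with 110 study samples and 12 QC samples, with the QC pool placed at the mean abundance:

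| Between-sample SD (log2) | Removed, true CV 10% | Removed, true CV 30% | Removed, true CV 100% |
|---|---|---|---|
| 0.3 | about 1% | 52% | 76% |
| 0.5 | 0% | 18% | about 70% |
| 1 | 0% | 0.1% | 36% |
| 2 | 0% | 0% | under 1% |
| 3 | 0% | 0% | 0% |

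A compound with a true CV of 100% therefore passes about 24% of the time at a spread of 0.3, and nearly always at a spread of 2 or more. Placing the QC pool at the log2 centre instead lowers the pass rate at a spread of 2 to about 94%.

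**Third possibility: the shift adds a positive offset back.** With an assumed offset of 10 log2 units, the cut-off falls at SD_log2 = 3, a raw CV of about 860%. This does not rescue the rule.

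**After the fix.** Taking the CV from the log2 SD of 12 QC samples gives median estimates of 0.097, 0.29 and 0.58 for true CVs of 0.10, 0.30 and 0.60. The cut-off then has the same meaning for every compound.

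**The case against.** The strongest reply is that the text does not fix Reading A. An analyst who saw nearly every compound disappear would notice, so the figures under that reading should not set the weight of the point. That stands.

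Under Reading B the ratio is QC noise relative to the distance to the lowest value. Because the data are later ranked within compound, noise relative to spread is arguably what matters. A simulation on these lines (110 samples, 12 QC samples, spread assumed) supports this in part:
- At a spread of 0.3 with raw CV 7%, the compound always passes, and its ranks correlate 0.94 with the truth.
- At the same spread with raw CV 69%, it passes 24% of the time, with correlation 0.30.
- At a spread of 2 with raw CV 69%, it passes 99% of the time, with correlation 0.90.

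Pass rates thus broadly follow rank reliability. A reader might infer that the filter keeps and drops compounds arbitrarily, or that tight, precise compounds are the ones lost. Under Reading B the document does not support either inference: the ratio rises with QC noise, and at a spread of 0.3 or more compounds with a true CV of 10% almost always pass.

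What the reply does not rescue is the label and the denominator. If noise relative to spread is the aim, a single lowest value is an unstable measure of spread, and very noisy compounds still pass about a fifth to a third of the time at spreads of 0.2 to 0.5.

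It may also be said that the code back-transforms, or that this is detail for an analysis plan. The article fixes the transformation, the shift, the statistic and the threshold, and section {31c} describes the paper as giving the protocol in full. If the code does something else, the text needs correcting all the same.

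**Conclusion.** The point holds in limited form. As written, the 0.3 cut-off does not hold assay CV to 30%. If the minimum is over the QC samples, the filter carries no information on precision and removes nearly everything. If it is over all samples, the filter does respond to QC noise, but the limit differs by compound: a raw CV of about 21% at a distance of 1 log2 unit, 69% at 3 and 193% at 6. It is lenient for wide-range compounds, stricter for narrow-range ones, and depends on one extreme value.

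The algebra behind both readings does not rest on assumed counts. The sizes do: the number of QC samples, the between-sample spread, normal log2 errors, and the reading of the shift as subtraction are all assumptions. The document gives no basis for saying how many compounds are affected, or that the primary result would change.

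**What to change.** In section {20c}, replace the shift and CV step with a CV on the abundance scale, computed from the batch-corrected log2 SD of the QC samples: CV = sqrt(exp((ln2 × SD_log2)²) − 1). Remove compounds with CV of 0.30 or more, which is SD_log2 of about 0.42 or more. Drop the minimum shift from this step.

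If a noise-to-spread filter suited to the ranking was intended, say so and define it as the QC SD relative to the SD of the study samples, not the distance to the minimum, with its own stated threshold.

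The cost is one sentence and one line of code. The list of retained compounds, and so the number of tests under the false discovery rate, may change. Samples are to be analysed in batch at study completion and recruitment was still open at the protocol date, so the rule could be settled before any compound list existed.
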